## Abstract

**Background:**

People who inject drugs (PWID) remain a high priority population under the federal Ending the HIV Epidemic initiative with 11% of new HIV infections attributable to injection drug use. There is a critical need for innovative, efficacious, scalable, and community-driven models of healthcare in non-stigmatizing settings for PWID. We seek to test a *Comprehensive-TeleHarm Reduction (C-THR)* intervention for HIV prevention services delivered via a syringe services program (SSP).

**Methods:**

The CHARIOT trial is a hybrid type I effectiveness-implementation study using a parallel two-arm randomized controlled trial design. Participants (i.e., PWID; n = 350) will be recruited from a syringe services program (SSP) in Miami, Florida. Participants will be randomized to receive either *C-THR* or non-SSP clinic referral and patient navigation. The objectives are: (1) to determine if the *C-THR* intervention increases engagement in HIV prevention (i.e., HIV pre-exposure prophylaxis; PrEP or medications for opioid use disorder; MOUD) compared to non-SSP clinic referral and patient navigation, (2) to examine the long-term effectiveness and cost-effectiveness of the *C-THR* intervention, and (3) to assess the barriers and facilitators to implementation and sustainment of the *C-THR* intervention. The co-primary outcomes are PrEP or MOUD engagement across follow-up at 3, 6, 9 and 12 months. For PrEP, engagement is confirmed by tenofovir on dried blood spot or cabotegravir injection within the previous 8 weeks. For MOUD, engagement is defined as screening positive for norbuprenorphine or methadone on urine drug screen; or naltrexone or buprenorphine injection within the previous 4 weeks. Secondary outcomes include PrEP adherence, engagement in HCV treatment and sustained virologic response, and treatment of sexually transmitted infections. The short and long term cost-effectiveness analyses and mixed-methods implementation evaluation will provide compelling data on the sustainability and possible impact of *C-THR* on comprehensive HIV prevention delivered via SSPs.

**Discussion:**

The CHARIOT trial will be the first to our knowledge to test the efficacy of an innovative, peer-led telehealth intervention with PWID at risk for HIV delivered via an SSP. This innovative healthcare model seeks to transform the way PWID access care by bypassing the traditional healthcare system, reducing multi-level barriers to care, and meeting PWID where they are.

*Trial Registration*: ClinicalTrials.gov NCT05897099. Trial registry name: Comprehensive HIV and Harm Prevention Via Telehealth (CHARIOT). Registration date: 06/12/2023.

## Introduction

### Background and rationale

Injection drug use (IDU) continues to be an important mode of transmission for HIV infection, and people who inject drugs (PWID) are a high priority population under the United States (US) Ending the HIV Epidemic initiative [1]. In 2020, 11% of new HIV infections were attributable to IDU [2]. IDU has led to multiple recent outbreaks of HIV in the US, driven primarily by the ongoing stimulant and opioid crises and exacerbated by the COVID-19 pandemic, creating an obstacle to meeting Ending the HIV Epidemic goals [3–8]. The Ending the HIV Epidemic initiative has identified evidence-based interventions including rapid HIV testing, antiretroviral therapy (ART), comprehensive syringe services programs (SSPs), and pre-exposure prophylaxis (PrEP) that need to be implemented, scaled, and sustained within communities most affected by HIV. To maximize the effectiveness of these interventions among PWID, comprehensive healthcare models must be developed, tested, and deployed where PWID are, in comfortable, non-stigmatized environments that simultaneously address a key driver of HIV, namely untreated substance use disorder (SUD).

PWID often experience pervasive discrimination, stigma, degradation and social disadvantage when accessing the traditional healthcare system, leading to almost universal poorer health outcomes compared to non-PWID [9–17]. However, one long-standing, trusted, and frequented institution for PWID are SSPs. Decades of research have highlighted their effectiveness in HIV prevention [18–23] and, more recently, their ability to implement HIV testing [24], PrEP [25], medications for opioid use disorder (MOUD) [26], and overdose education and naloxone distribution [27]. Increased access to MOUD has been shown to facilitate positive care outcomes among people with opioid use disorder (OUD) [28, 29], and SSPs have been shown to be ideal venues to offer PrEP [30] and buprenorphine [31–33] to further mitigate HIV risk and acquistion. However, initiating and retaining PWID on PrEP and MOUD remains a major implementation challenge, limiting our ability to meet Ending the HIV Epidemic targets. Multiple studies have demonstrated significant gaps in the PrEP cascade for PWID, leading to extremely low uptake, initiation, and persistence on PrEP (0–3%) [34–36]. Likewise, the OUD care cascade has pervasive gaps, with low rates of OUD screening, MOUD initiation, and MOUD retention among PWID [37]. Questions remain on how to most effectively implement sustainable and scalable integrated HIV prevention and OUD care models in SSPs for PWID.

We developed, refined, and pilot tested *tele-harm reduction (THR)*: a telehealth-based, multicomponent care model for PWID with HIV implemented at the IDEA Miami SSP. *THR* integrates multilevel stigma reduction [38, 39] and harm reduction frameworks [40] to provide access to HIV care through telehealth in an SSP setting that is supported by on-site peer-driven systems of care to enhance treatment initiation and adherence. *THR* has preliminarily demonstrated high acceptability and promising outcomes with 78% of PWID with HIV achieving viral suppression at 6 months post-enrollment, significantly higher than current national estimates which show 56.9% of PWID are virally suppressed [2, 40–42]. Our interdisciplinary research team is currently testing the efficacy of the *THR* model for HIV viral suppression in a randomized controlled trial (RCT) under a National Institute on Drug Abuse Avenir Award (DP2DA053720, PI: [name]).

Building upon this work of *THR* for HIV treatment in PWID and in pursuit of a status neutral [43] intervention for comprehensive HIV care, we developed *comprehensive tele-harm reduction (C-THR)* to address HIV prevention in this high priority community. The overall goal of the CHARIOT trial is to compare the efficacy of the *C-THR* intervention in engaging PWID in HIV prevention services (i.e., PrEP and/or MOUD) to current standard of care (i.e., non-SSP clinic referral and patient navigation) using a parallel two-arm RCT, and evaluate the process of implementation consistent with the aims of a hybrid type I effectiveness-implementation study [44].

### Objectives

The first objective of the study is to compare the efficacy of the *C-THR* intervention for engagement in HIV prevention services (i.e., PrEP and MOUD) versus non-SSP clinic referral and patient navigation, with the co-primary outcome the time averaged proportion of participants engaged with PrEP or MOUD across follow-up at 3, 6, 9 and 12 months. For PrEP, engagement is confirmed by tenofovir on dried blood spot or cabotegravir injection within the previous 8 weeks. For MOUD, engagement is defined as screening positive for norbuprenorphine or methadone on urine drug screen (UDS); or extended release buprenorphine or naltrexone injection within the previous 4 weeks. The primary hypothesis is that C-THR will be superior to non-SSP clinic referral and patient navigation in promoting engagement of PWID in HIV prevention.

In relation to the primary objective, we will also measure differences between study arms in several secondary outcomes including syringe coverage, PrEP adherence, engagement in hepatitis C virus (HCV) treatment, rates of HCV cure, treatment of sexually transmitted infections (STIs), time to injection-related harm and number of injection-related harms. Participants in the C-THR arm will have peer-facilitated enhanced access to a physician via a telehealth platform, phlebotomy at both fixed and mobile sites, peer-facilitated medication management (e.g., storage in pill lockers at SSP, weekly delivery), appointment reminders, and mental health counseling. Participants assigned to the non-SSP clinic referral and patient navigation arm will be linked to a community health center or primary care clinic (e.g., Federally Qualified Health Center) by SSP staff as is the current standard of care with patient navigation for the first clinic visit.

The second objective of the study is to estimate the short- and long-term clinical- and cost-effectiveness of *C-THR* versus non-SSP clinic referral and patient navigation. The economic analysis will follow best practices for conducting economic analyses alongside clinical trials [45–47]. The long-term clinical and cost-effectiveness will utilze a validated simulation model [48, 49]. The REDUCE model was designed to simulate the natural history of IDU and understand how both hospital- and community-based interventions designed to *reduce* injection frequency and *reduce* risky injection behaviors (e.g., decrease needle reuse) may improve long-term outcomes.

The third objective of the study is to assess the implementation context (ie. barriers and facilitators) to successful *C-THR* implementation in an SSP setting and evaluate the process of implementation over the course of the study. Our mixed-methods implementation evaluation will leverage the Practical, Robust Implementation and Sustainability Model (PRISM) to understand how external and internal contextual factors influence reach, implementation, and maintainence of *C-THR.*

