### Eligibility criteria

Eligibility criteria include the following: (1) age 18 or older; (2) able to speak English or Spanish; (3) willing and able to sign informed consent, provide locator information and medical records release; (4) non-reactive result on rapid HIV test; (5) use of SSP to exchange syringes two times in the past 3 months; and (6) planning to stay in the area for 12 months. Of note, pregnant people are eligible for enrollment in this trial but will not be purposely recruited.

Exclusion criteria include the following: (1) PWID with HIV; (2) currently on MOUD; (3) currently on PrEP; (4) principal or site investigator discretion; (5) currently in prison or jail; and (6) current enrollment in NIDA Clinical Trials Network (CTN) 121 which is a study that our team is leading in Miami to test a comprehensive, integrated hospital-based intervention to address concurrent treatment and follow-up support for PWID with severe infections; (7) current enrollment in M2HepPrEP (R01 DA045713) [52] which is an integrated Hepatitis C and HIV prevention study that our team is completing this year; (8) hepatitis B surface antigen positive; (9) receipt of *THR* in the previous 3 months; and (10) signs or symptoms of acute HIV infection. Investigator discretion could include serious medical, psychiatric, or co-occurring SUD that acutely requires a higher or different level of care including the following: (1) disabling or terminal medical illness (e.g., decompensated heart failure); (2) severe, untreated or inadequately treated psychiatric condition (e.g., active psychosis); (3) in need of medical detoxification for severe alcohol, benzodiazepine, or other depressant or sedative hypnotic use; (4) suicidal intent or plan; and (5) homicidal ideation.

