### Outcomes

Table 1 shows the primary and secondary outcomes of objective 1. The co-primary outcomes will be engagement in HIV prevention via PrEP and/or via MOUD. PrEP engagement will be measured by intracellular levels of TFV-DP on DBS or abstraction of a cabotegravir injection in the previous 8 weeks. MOUD engagement will be measured by norbuprenorphine or methadone on UDS or abstraction of a naltrexone or buprenorphine injection in the previous 4 weeks.

**Table 1 Tab1:** Primary and secondary outcomes for objective 1

	Definition	Measure
Primary outcome		
HIV Prevention via PrEP	Taking PrEP at 3-, 6-, 9-, and 12-month follow-up	Intracellular levels of tenofovir diphosphate (TFV-DP) by DBS or cabotegravir injection in previous 8 weeks by electronic health record abstraction
HIV Prevention via MOUD	Taking MOUD at 3-, 6-, 9-, and 12-month follow-up	Norbuprenorphine or methadone on UDS or naltrexone or buprenorphine extended-release injection in previous 4 weeks by electronic health record abstraction
Secondary outcomes		
Syringe coverage	Dispensing syringes to cover each injection event	Number of syringes distributed/(number of injections per day × days between exchanges) from SSP administrative data
PrEP Adherence	Taking PrEP at least 4 times per week	TFV-DP level of 700 fmol/punch on DBS for TDF [64]; TFV-DP level of 950 fmol/punch on DBS for TAF[65]
Engagement in HCV treatment	Receiving a prescription for DAA	DAA prescsiption confirmed on electronic health record abstraction
HCV cure (SVR 12)	Initiating HCV treatment and achieving undetectable HCV RNA PCR at least 12 weeks after completion of therapy	Negative HCV RNA PCR (viral load) at least 12 weeks post treatment completion
Treatment of STIs	Receiving treatment for STI after a positive screen	Prescription of appropriate antibiotics (may differ based on allergies) from electronic health record abstraction
Time to harm	Time to: (1) emergency department visit or hospitalization for injection-related infection or overdose; (2) incident HIV infection; (3) incident HCV infection; or (4) death from overdose	(1) Electronic health record abstraction; (2, 3) IDEA test results; (4) electronic health record abstraction or medical examiner database

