**Table 3 Tab3:**
[figure not shown]
Assessment schedule

All participants will complete laboratory assessments at screening and at 3-, 6-, 9- and 12-month follow-up assessments. At screening, this will include rapid HIV test by fingerstick and point of care urine screens for tenofovir, buprenorphine, and methadone to determine eligibility. Additional tests at screening include fourth generation HIV test, HCV RNA, STI screens, hepatitis serologies, comprehensive metabolic panel, complete blood count and, as indicated, urine pregnancy test. At baseline and at 3-, 6-, 9- and 12-month follow-up assessments, these will include urine drug screen for buprenorphine/norbuprenorphine and methadone/EDDP (methadone metabolite) and fingerstick DBS to test for both the presence and therapeutic levels of TFV-DP related to the primary outcome, as well as HIV Ag/Ab screen, HCV RNA, HIV/HCV rapid tests, and STI screen (including syphilis via blood and gonorrhea/chlamydia via throat swab, rectal swab, and urine). Additionally, participants in the *C-THR* arm will also have a creatinine assessment at 6 and 12 months.

To confirm primary outcome by medical record abstraction, the electronic health record will be quieried for date of injection of (1) cabotegravir, (2) naltrexone or (3) buprenorphine. A cabotegravir injection in the previous 8 weeks will be considered as having met the primary outcome. A naltrexone or buprenorphine injection in the previous 4 weeks will be considered as having met the primary outcome.

The cost and cost-effectiveness analysis will consist of an economic evaluation of *C-THR* versus non-SSP clinic referral and patient navigation from both the healthcare sector perspective and the modified societal perspective. Specifically, the evaluation will focus on budgetary impact and cost-effectiveness to inform application of *C-THR* locally and nationally. This evaluation will follow recommendations of the 2nd Panel on Cost Effectiveness in Health and Medicine [45], Glick et al. [46] and Drummond [47].

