##### *Hypothesis 1*

*C-THR* will be superior to non-SSP clinic referral and patient navigation in promoting engagement in HIV prevention as measured by the proportion of participants taking PrEP and/or MOUD across follow-up at 3, 6, 9 and 12 months post-randomization.

### Primary inferential analyses to address primary hypothesis of objective 1

We hypothesize that, for those randomized to the *C-THR* arm, the odds of our two co-primary outcomes, engagement in PrEP and engagement in MOUD, will be higher than for those randomized to the non-SSP clinic patient navigation, control arm (Hypothesis 1). Generalized estimating equations (GEE) [92] will be used to perform the proposed primary analysis, which is a planned time-averaged comparison of all post-baseline measurements of the each of these outcomes—PrEP: DBS evidence of tenofovir or cabotegravir injection in the previous 8 weeks by electronic health record abstraction; MOUD: UDS with norbuprenorphine or methadone/EDDP; or naltrexone or buprenorphine injection in previous 4 weeks by electronic health record abstraction—across the *C-THR* and control groups to test primary Hypothesis 1. Alpha will be set at 0.025 for this planned comparison to control the Type-1 error across these two co-primary outcomes. In each model, recruitment site (fixed site vs. mobile site) and OUD diagnosis (yes vs. no) will be included in these analyses as required by the stratified randomized design to obtain unbiased results. If the overall test of the intervention is statistically significant, individual contrasts for differences between the conditions at each of the times of follow-up will be performed.

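### The PrEP co-primary counts any tenofovir on DBS at any visit with no HIV-status condition, so a participant treated for new HIV infection with tenofovir would be scored as engaged in PrEP

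*Protocol article*

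**What the plan says.** Three places in the protocol article give the operative definition of PrEP engagement, and they agree.

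- Objectives: "For PrEP, engagement is confirmed by tenofovir on dried blood spot or cabotegravir injection within the previous 8 weeks".
- Outcomes, Table 1, measure column: "Intracellular levels of tenofovir diphosphate (TFV-DP) by DBS or cabotegravir injection in previous 8 weeks by electronic health record abstraction". The definition column beside it describes the outcome as taking PrEP at the four follow-up visits.
- Primary inferential analyses under Hypothesis 1: "PrEP: DBS evidence of tenofovir or cabotegravir injection in the previous 8 weeks by electronic health record abstraction". The comparison is a "planned time-averaged comparison of all post-baseline measurements".

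The co-primary carries no concentration cut-off. The thresholds of 700 and 950 fmol/punch belong to the secondary adherence outcome.

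HIV status is a condition at entry only. Eligibility requires "4) non-reactive result on rapid HIV test", and people with HIV are excluded. During follow-up, Table 1 counts "2) incident HIV infection" among the harms, both for time to harm and for number of harms.

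Under Plans for assessment and collection of outcomes, an HIV Ag/Ab test is done at 3, 6, 9 and 12 months, at the same visits as the "fingerstick DBS to test for both the presence and therapeutic levels of TFV-DP related to the primary outcome". Record abstraction for the primary outcome covers dates of injections only, so the purpose of an oral tenofovir prescription is not checked.

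**The concern.** The assay detects the drug and not the reason for taking it. At entry this does no harm, because everyone is HIV-negative. After a seroconversion the same DBS result can reflect treatment of an established infection, and the stated measure cannot tell the two apart. The measure then departs from Table 1's own definition of the outcome. The same person could be a success on a co-primary outcome and a harm on two secondary outcomes.

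What is at stake is a wrong classification in a co-primary outcome. The trial is open-label. If the rule is not set in advance, someone must decide how to score these visits when the arm of each seroconverter may already be known.

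**Working it through.** **Inputs from the article (Sample size).** 350 participants allocated 1:1, so 175 per arm. Expected numbers at the four visits are 315, 284, 255 and 230, or 157.5, 142, 127.5 and 115 per arm, a total of 542 person-visits per arm. The control proportion is 30%, stated for PrEP or MOUD. Alpha is 0.025 and power 0.80. The minimum detectable difference is 0.101 (OR 1.56).

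**Inputs assumed.** HIV incidence of 1 to 3 per 100 person-years, and every seroconverter on a tenofovir-containing regimen. The article gives neither.

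**Reproducing the plan's figure.** With exchangeable correlation ρ, a participant seen k times contributes k/(1+(k−1)ρ). Per arm, 15.5, 14.5, 12.5 and 115 participants are seen 1, 2, 3 and 4 times. At ρ = 0.10:

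15.5×1 + 14.5×1.818 + 12.5×2.5 + 115×3.077 = 427 effective observations per arm.

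For 30% against 40.1%, OR = (0.401/0.599)/(0.30/0.70) = 1.562 and log OR = 0.446. The standard error is √[1/(427×0.30×0.70) + 1/(427×0.401×0.599)] = 0.1446. For two-sided alpha 0.025 the required log OR is (2.241+0.842)×0.1446 = 0.446. The stated 0.101 and 1.56 reproduce, and the present point does not change them.

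**Seroconverters.** 175 × 1 to 3% = 1.75 to 5.25 per arm with full follow-up.

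**Misscored visits, treatment visible from the visit after detection.** Infections arising before 3, 6 and 9 months are misscored at 6, 9 and 12 months. At 1 per 100 person-years the shares are 0.25%, 0.50% and 0.75%:

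142×0.0025 + 127.5×0.0050 + 115×0.0075 = 0.36 + 0.64 + 0.86 = 1.86 visits, and 1.86/542 = 0.34%.

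At 3 per 100 this triples to 5.6 visits, or 1.03%.

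**Ceiling, treatment already visible at the visit where infection is found.**

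157.5×0.0025 + 142×0.0050 + 127.5×0.0075 + 115×0.0100 = 3.2 visits, or 0.59%.

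At 3 per 100 this is 9.6 visits, or 1.8%.

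**Effect on the contrast.** If a share m of visits is misscored in an arm with true proportion p, the observed proportion rises by (1−p)m. The table takes the assumed incidence in the control arm and none in the other.

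| Case | m | Shift, p = 0.30 | Shift, p = 0.03 |
|---|---|---|---|
| Visit after detection, 1 to 3 per 100 | 0.34 to 1.03% | 0.002 to 0.007 | 0.003 to 0.010 |
| Ceiling, 1 to 3 per 100 | 0.59 to 1.8% | 0.004 to 0.012 | 0.006 to 0.017 |

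With equal incidence in both arms, the difference is multiplied by (1−m): 0.101×(1−0.0103) = 0.100.

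As a stress test, assumed incidences of 5 and 10 per 100 person-years give a ceiling m of about 2.9% and 5.7%. The one-arm shifts at p = 0.30 are then 0.020 and 0.040.

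**Relative size.** If true PrEP use among controls were 3%, the top of the range in Background and rationale, the visit-after-detection case adds 0.0033 to 0.0100 to 0.03, a time-averaged relative rise of 11 to 33%. At 12 months alone it adds 0.97×0.75% to 0.97×2.25%, a relative rise of 24 to 73%. At 30% the 12-month rise is 0.7×0.75% to 0.7×2.25%, or 0.5 to 1.6 percentage points.

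**The case against.** The strongest reply is that Table 1 separates definition from measure. The definition is taking PrEP, which someone treated for HIV is not doing. What is left is a coding rule for a rare event, and that is normal content for an analysis plan. The section on blinding says such a plan will be confirmed before data lock, and it is not shown here.

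Part of this stands. An unseen plan may contain the rule, and the definition column shows what was intended. But the article is not silent on scoring. It states the scoring rule three times, applies it to all post-baseline measurements, and the rule as written gives the wrong class for these participants. The objection is to what is stated.

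It is also fair that the mechanism needs several things the article does not supply: infection, diagnosis, a treatment start, a tenofovir-containing regimen, continued use and retention. The figures above set all the treatment steps at 100%, so they are upper limits for each assumed incidence.

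A reader might draw stronger conclusions, which the documents do not support.

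- **That C-THR's benefit will be masked.** This needs C-THR to lower HIV incidence within 12 months and treatment uptake to be similar in both arms. Neither is established. The SSP already runs a tele-harm reduction model for HIV treatment, so treated seroconverters could be more common in either arm.
- **That the control proportion will be inflated by a quarter or more.** That holds only near the last visit and with true control use of about 3%. The outcome is time-averaged. The background report of "extremely low uptake, initiation, and persistence on PrEP" describes people who inject drugs in other studies, whereas trial controls get scheduling, transport and accompaniment to a first clinic visit. The article gives no PrEP-only control rate, so the low-use case is neither shown nor excluded.
- **That the power calculation is affected.** The stated detectable difference reproduces and does not depend on this point.

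**Conclusion.** The point holds as a defect in the written endpoint, of minor weight. The PrEP co-primary measure would score a treated seroconverter as engaged, against the outcome's own definition.

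Under an assumed incidence of 1 to 3 per 100 person-years, with universal tenofovir-containing treatment from the visit after detection, about 0.3 to 1.0% of person-visits per arm are misscored. The shift in the time-averaged difference is about 0.01 at most with infections in one arm only, and about 0.001 with equal incidence. Incidence well above that range, or very low true PrEP use, would make it matter more. The direction is unknown in advance: engagement is overstated in whichever arm has more treated infections.

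**What to change.** Add one scoring rule to the co-primary definition: from the first visit with confirmed HIV infection onwards, the participant counts as not engaged in PrEP whatever the DBS shows, and stays in the denominator. Add a sensitivity analysis that excludes those visits. This also covers the detection visit itself, where tenofovir on DBS may still reflect genuine PrEP use.

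The rule should be fixed before outcome data are examined by arm. It costs a sentence or two and one extra model run. HIV Ag/Ab and DBS are already collected at every follow-up visit, and the rule changes no treatment, visit schedule or sample size.
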